## Abstract

**Background:**

Long-Lasting Insecticidal Nets (LLINs) are one of the major malaria vector control tools, with most countries adopting free or subsidised universal coverage campaigns of populations at-risk from malaria. It is essential to understand LLIN durability so that public health policy makers can select the most cost effective nets that last for the longest time, and estimate the optimal timing of repeated distribution campaigns. However, there is limited knowledge from few countries of the durability of LLINs under user conditions.

**Methods/Design:**

This study investigates LLIN durability in eight districts of Tanzania, selected for their demographic, geographic and ecological representativeness of the country as a whole. We use a two-stage approach: First, LLINs from recent national net campaigns will be evaluated retrospectively in 3,420 households. Those households will receive one of three leading LLIN products at random (Olyset^®^, PermaNet^®^2.0 or Netprotect^®^) and will be followed up for three years in a prospective study to compare their performance under user conditions. LLIN durability will be evaluated by measuring Attrition (the rate at which nets are discarded by households), Bioefficacy (the insecticidal efficacy of the nets measured by knock-down and mortality of mosquitoes), Chemical content (g/kg of insecticide available in net fibres) and physical Degradation (size and location of holes). In addition, we will extend the current national mosquito insecticide Resistance monitoring program to additional districts and use these data sets to provide GIS maps for use in health surveillance and decision making by the National Malaria Control Program (NMCP).

**Discussion:**

The data will be of importance to policy makers and vector control specialists both in Tanzania and the SSA region to inform best practice for the maintenance of high and cost-effective coverage and to maximise current health gains in malaria control.

**Electronic supplementary material:**

The online version of this article (doi:10.1186/1471-2458-14-1266) contains supplementary material, which is available to authorized users.

## Background

The recent successes in malaria control in sub-Saharan Africa (SSA), specifically in Tanzania where malaria deaths have reduced by 70% since 2003, has been largely attributable to the massive scale up of vector control tools, particularly Long Lasting Insecticidal Nets (LLINs) [1–3]. However, sustained malaria control is costly, and dependent on continuing political and donor support. As political commitment diminishes, the deliveries of life-saving control tools will slow down and risk the reversal of the huge achievements to date. Global commitments for malaria control in 2012 were approximately US$2.5 billion, far below the estimated sum of US$5.1 billion required for the task [4]. Global funding mechanisms are projected to decelerate even further in the coming years, leaving gaps of US$2.25 billion before achieving universal access to malaria interventions [1]. Therefore, maximising the impact of interventions through selection of the most cost effective and long lasting interventions is a health policy priority.

Despite the huge financial and logistical investments in the development, production and distribution of LLINs worldwide, there are still limited data available on the LLIN durability under user conditions. The World Health Organization (WHO) released specific guidance on LLIN durability monitoring [5, 6], which was incorporated into guidelines for laboratory and field-testing of LLINs [7] to support national governments with the design of standardised net monitoring and evaluation studies. Effective net life has been estimated to be 3-5 years [8], but some studies indicate that LLIN brands may last less than three years under operational conditions [9–12]. It is only recently that researchers have started to investigate net attrition, i.e. how long nets remain in use in a household, and constructed net survivorship curves [5, 13]. Durability of mosquito nets should thus be defined and measured by the whole process of net loss – from attrition and physical damage to the chemical loss of insecticide residue [5].

Net deterioration differs greatly between regions or cultures as care and repair behaviours, maintenance and net use vary from place to place. Thus, nation-wide evaluations of LLINs are required and called for by the WHO [6, 14]. Evaluation of PermaNet^®^2.0 retrieved from six countries [15] and Olyset^®^ nets from seven countries [16] show large between-country variability of LLIN durability. Net products also vary in material, insecticide, or fibre impregnation technology. Such variations are still largely unknown and direct comparisons within sites are scarce [17] (but see [9, 11, 18]). Reliable data need to be collected by National Malaria Control Programs (NMCPs) to inform national procurement decisions for 1) selection of the most suitable net to plan timely replacement, 2) to understand factors associated with net durability to guide behaviour change communication including care and repair interventions, and 3) to assist industry in product improvement. NMCPs need to understand LLIN durability in their local settings because replacing nets too late puts people at risk of disease, but replacing them too often wastes limited resources.

Also, the dramatic increase in pyrethroid resistance in mosquitoes throughout SSA, including Tanzania [19], might be posing a threat to the sustainability of insecticidal control methods [20, 21]. A surveillance system to monitor emerging insecticide resistance, for example using Geographical Information Systems (GIS) [22, 23], would allow governments and national malaria control programmes to plan resistance control strategies [24]. Spatio-temporal analysis of malaria transmission to identify persistent transmission hotspots may maximise cost- and health-effectiveness of control programmes [23]. The determinants and risk factors for net loss and effectiveness vary spatially, but there is a lack of information of which factors play a role in the attrition and deterioration of LLINs.

Therefore, the current study is conducted in collaboration with the Tanzanian NMCP to inform their procurement decisions. The study will be conducted in eight districts in Tanzania, selected for their demographic, geographic and ecological representativeness of the country as a whole. There will be an initial retrospective evaluation of Olyset^®^ nets distributed by the NMCP two-to-four years previously as part of both a targeted and a universal coverage campaign [25]. The same sampled households will then receive one of three LLIN products (Olyset^®^ with the new knit pattern to improve fabric strength, PermaNet^®^2.0 or Netprotect^®^) by random allocation for a prospective follow up study. Effective life of the nets will be assessed at regular intervals for three years using the WHO-recommended set of net durability variables [5] (Table 1) and a set of new methodologies (Figure 1). We will also monitor insecticide resistance in mosquito vectors as an additional component for evaluating LLIN effectiveness to contribute to the growing knowledge within Tanzania, which will assist the NMCP on rational selection of insecticides for vector control. Spatial risk factors of insecticide resistance and LLIN durability, such as land use patterns, agriculture, altitude or distance to potential breeding sites, will be assessed to determine their usefulness in selecting appropriate malaria control strategies by identifying areas where a particular LLIN intervention may be more effective than another.

**Table 1 Tab1:** **LLIN durability components**

Component	Definition	Response variables for analysis
**A**ttrition	Net loss from household through discarding or use for alternative purpose	- Net presence.
**B**iological efficacy	Ability of net to incapacitate or kill anopheline mosquitoes after contact with insecticide	- Mosquito knockdown (%) 60 minutes post-exposure.
		- Mosquito mortality (%) 24 hours post-exposure.
		- Percentage of bloodfed mosquitoes.
**C**hemical residue	Amount of active ingredient in fibres	- Proportion of nets with active ingredient equal to WHO standard g/kg
**P**hysical degradation	Physical state of the net defined through number, size and location of holes to estimate protection against mosquito bites	- Proportionate Hole Index (pHI) / hole area by location on net.
		- Proportion of nets with a pHI exceeding ≥643 [6].

**Figure 1 Fig1:**
[figure not shown]
**Flow chart of retrospective and prospective data collection.** After study district and village selection, 45 households will be randomly selected from each village for study inclusion. After obtaining national ethical approval, community sensitisation meetings will be held and written informed consent will be obtained from each household head participating in the study. In the retrospective study in 2013, all nets from study households will be removed after an in-depth household questionnaire and 200 Olyset campaign nets will be sub-sampled for laboratory analysis of LLIN durability components (Table 1). All collected nets will be replaced with one of three new LLIN products; Olyset^®^, PermaNet^®^2.0 and Netprotect^®^ (Table 2) for the prospective study. Ten, 22 and 36 months post-distribution, every household will be followed up with a questionnaire and the presence of each study net will be affirmed to obtain attrition estimates. A random sub-sample of 48 nets per net product will be collected for subsequent analyses consisting of Ifakara Tunnel Tests, hole counts, biological efficacy tests and HPLC analysis.

## Methods/Design

### Study population

The project will be carried out in eight districts representing five of the eight geographical zones of Tanzania and covering variations in malaria epidemiology and ecology. Fifteen districts, i.e. seven districts in addition to the eight previously mentioned, will be included in the mosquito insecticide resistance part of the project (Figure 2). The 15 districts were selected from the 23 districts enrolled in the population arm of the Sentinel Panel of Districts (SPD), SAmple Vital registration with Verbal autopsY (SAVVY) [26]. The 23 SAVVY districts were selected using two-stage sampling with probability proportional to size (PPS) of districts and villages/Enumeration Areas (EAs) from the 2002 Population and Housing Census dataset [27]. In each of the eight districts (Figure 2), all households within 6-20 villages/EAs were enrolled by the SAVVY programme for national representativeness in 2012/2013. We will select ten SAVVY villages per district based on the proximity to district headquarters, except for Kinondoni (Dar es Salaam) where SAVVY only covered six EAs. Using the SAVVY baseline household information, 45 households per village will be randomly selected using the ‘sample’ function in the statistical software R 3.1.1 [28], giving a total of 3,420 households nationwide. Fifty percent more households will be randomly selected as substitution households to accommodate for non-consent or household head absence. The 3,420 study households will be geo-referenced using Global Positioning System (GPS) points to create a GIS database including data on village and house characteristics, socioeconomic variables, net characteristics, and geographical variables, such as environment, land use and potential mosquito breeding sites.

**Figure 2 Fig2:**
[figure not shown]
**ABCDR study districts in Tanzania.** Districts selected for LLIN durability (ABCD-components) and the insecticide resistance part of the project (R-component) with malaria prevalence data (% of children aged 6-59 months diagnosed with malaria by Rapid Diagnostic Test and microscopy [29]) and geographical zone. The following eight districts are included in the LLIN study: Kinondoni (1), Mbozi (5), Iringa Urban (6), Kilosa (7), Bagamoyo (8), Geita (12), Musoma Rural (13) and Kahama (14).

### LLIN products

All three products (Table 2) that will be tested in the prospective study were recommended by WHO Pesticide Evaluation Scheme (WHOPES) at the point of procurement with full approval of Olyset^®^
[16] and PermaNet^®^2.0 [15], and interim approval of Netprotect^®^
[30]. However, Netprotect^®^ approval was withdrawn in September 2014 [31] and from that point on it was decided to replace all sub-sampled study Netprotect^®^ nets with Olyset^®^. The WHOPES working group recommends that programmes should monitor efficacy and performance of Netprotect^®^ under local conditions to obtain further information about the product [32]. Ten nets of each product will be assessed at baseline to ensure that they meet WHOPES thresholds for bioefficacy against anopheline mosquitoes using WHO cone and tunnel tests and insecticidal content with high-performance liquid chromatography (HPLC) analysis.

**Table 2 Tab2:** **Characteristics of Olyset**
^**®**^
**, PermaNet**
^**®**^
**2.0 and Netprotect**
^**®**^
**net products distributed in the study**

Product name	Product type	Insecticide concentration	Denier	Manufacturer	WHO approval	Reference
Olyset^®^	Permethrin **incorporated** into polyethylene	780 mg/m^2^	>150 denier	Sumitomo Chemicals	Full	[16]
PermaNet^®^ 2.0	Deltamethrin **coated** on polyester	55 mg/m^2^	100 denier	Vestergaard Frandsen	Full	[15]
Netprotect^®^	Deltamethrin **incorporated** into polyethylene	68 mg/m^2^	110 denier	BestNet	Withdrawn	[30, 31]

As a consequence of using LLIN products from different materials (Table 2), the nets may be able to be distinguished physically. However, each net type will be rectangular, of the same dimensions (190 cm x 180 cm x 150 cm) and colour (white) with six loops per net to prevent household participants, technical staff and field team from knowing the treatment allocation as much as possible. A waterproof unique identifying barcode and a five-digit serial number will be attached to each distributed LLIN with a self-laminating laser tag to a hanging loop of the net. This will allow tracking of the nets once they are distributed. The field team will record the net serial number on the questionnaire as the net is distributed to allow the matching up of household and unique net identifying numbers on the net master list.

### Study design

The general study design is shown in a flow chart in Figure 1. One week before the start of the study, a sensitisation meeting will be set up at the district level to inform community leaders (Mwenyekiti and Viongozi), key informants, District Executive Directors (DEDs) and District Medical Officers (DMOs) of the purpose and design of the study. Their permission to work within the community will be sought to inform the community members of the study’s objectives and methods.

#### Retrospective study

Households will be enrolled on written informed consent (Additional file 1). Participants’ houses and questionnaires will be identified by barcodes associated with numeric codes (six-digit serial numbers) to ensure their anonymity and due care will be taken to ensure that only barcodes and numeric codes are used on LLINs and questionnaires, thus blinding participants and researchers to treatment allocation. All the nets from the participating households will be collected and replaced with one of the three new LLIN products (Table 2) chosen at random. The prospective LLIN products will only be known to field teams as net types 1, 2 and 3, thereby blinding and randomising the treatment distribution as much as possible. Each day the field team will receive a household list and a randomly mixed bundle of five sets of type 1, 2 and 3 nets (three nets of same type per set bagged for one household, assuming an average of three sleeping spaces per household). The interviewer will randomly pick one set from the bundle to be distributed when they arrive at each household (modified lottery method). If the household contains more than three sleeping spaces, more nets of the same type will be provided. The interviewer will record the five-digit serial numbers attached to the nets on the questionnaire as described above. Thus, randomisation is conducted by the field workers at the household level, resulting in 15 households per village receiving sufficient nets of one product to cover each sleeping space (Table 3).

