## Current study status

At the time of submission of this manuscript (December 2014), the study had completed the retrospective data collection and random distribution of the three new LLIN products, the establishment of the return net data base, and the prospective household survey after 10 months.

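### The interviewer hand-picks the net set on arrival from coded, possibly distinguishable types with no concealment described, so allocation can be steered, and the per-survey brand test names no covariate to guard against it

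*Protocol article*

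**What the plan says.** The Retrospective study section describes the allocation. Each day the field team receives a household list and "a randomly mixed bundle of five sets of type 1, 2 and 3 nets", with "three nets of same type per set bagged for one household". Then "The interviewer will randomly pick one set from the bundle to be distributed when they arrive at each household", which the protocol calls a modified lottery. It adds that "randomisation is conducted by the field workers at the household level, resulting in 15 households per village" for each product. Households with more than three sleeping spaces receive further nets of the same type.

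On masking, "The prospective LLIN products will only be known to field teams as net types 1, 2 and 3". The LLIN products section matches shape, size, colour and number of loops, but says that because of the different materials "the nets may be able to be distinguished physically". Table 2 lists one polyester and two polyethylene products, of 100, 110 and more than 150 denier.

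The Data analysis section plans a logistic regression at each of the three surveys to compare attrition between products. Brand is the only term it names, and pairwise comparisons follow if the overall result is significant. The same section also plans multivariable generalised linear and mixed models to find what affects durability.

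The Current study status section reports that "the study had completed the retrospective data collection and random distribution of the three new LLIN products".

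**The concern.** The person who chooses the set is the person standing in front of the house. Calling the products 1, 2 and 3 hides the brand name, but it does not hide which type is being picked. Topping up with the same type also requires that type can be identified in the field. If an interviewer comes to favour one type for some houses, by apparent wealth, building type or family size, the arms will differ in things that may drive wear and discarding. The fixed number of sets per type balances how many households get each product, not which households.

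The brand comparison on attrition is the primary comparison and is meant to inform national procurement. As worded, it has no term that would absorb such an imbalance.

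**Working it through.** **1. The plan's own counts.** Inputs from Study population and Table 3: seven districts with 10 villages, one with 6, and 45 households per village.
- Villages: 7 × 10 + 6 = 76.
- Households: 76 × 45 = 3,420. Per product: 76 × 15 = 1,140. Both match Table 3.
- Reading the daily bundle as five sets of each type gives 15 sets, so three bundles fill a village at 15/15/15. The text does not state this split in so many words, but it fits Table 3.

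**2. How much choice the procedure leaves.** Take a 5/5/5 bundle drawn without replacement.
- Fully determined picks at the end of a bundle: the five sets of a given type fall at random into the 11 gaps around the other ten, so on average 5/11 of them come after all the others. Over three types this is 3 × 5/11 = 15/11 = 1.36 households.
- Households with at least two types still available: 15 − 1.36 = 13.64 on average, computed under random drawing.
- Predictability for someone who tracks the types used: let E(a,b,c) be the expected number of correct guesses with a, b and c sets left, and n = a + b + c. Then E(a,b,c) = max(a,b,c)/n plus the average of E over the next draw. This gives E(5,5,5) = 7.46 of 15, or 49.7%, against 33.3% with no information.

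The middle figure matters most: at about 13.6 of 15 doors there is a real choice to make. The determined picks at the end leave no choice of set.

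**3. What an imbalance would do.** No figure in the protocol fixes its size, so all inputs here are assumptions.

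False brand difference = (difference between arms in the share of hard-wearing households) × (attrition gap between hard-wearing and other households).

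| Imbalance between arms | Gap 10 points | Gap 20 points |
|---|---|---|
| 5 points | 0.5 | 1.0 |
| 10 points | 1.0 | 2.0 |
| 15 points | 1.5 | 3.0 |

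The upper imbalance corresponds, for example, to 30% hard-wearing households overall with 40% in one arm. The other two arms then average (3 × 30 − 40)/2 = 25%, a contrast of 15 points.

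The Sample size calculation section works with 47.5% versus 52.5%, a difference of 5 points. The range is thus 0.5/5 = 10% to 3/5 = 60% of that difference.

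**The case against.** The strongest reply is that this is a disclosed field compromise with several safeguards. Sets are bagged and the bundle is mixed. Brand names are withheld, and the nets match in size, colour and loops. Households are drawn in R and supplied as a daily list. Counts are balanced within each village, so village-level confounders are largely controlled by design. No motive is given for staff who know only codes. Reaching the upper imbalance in the table would mean placing about 114 extra hard-wearing households (10% of 1,140) in one arm. An article may also omit the opacity and labelling of the bags. All of this stands, and it makes large steering less likely. It does not change the stated rule that the interviewer selects the set by hand at the household.

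A reader might infer more than the documents support:
- **That the pick follows the interview.** Figure 1 says "all nets from study households will be removed after an in-depth household questionnaire", which times the removal of old nets. The pick is placed on arrival. The interviewer sees the house first, but answers to the questionnaire cannot be assumed to inform the pick.
- **That the types are plainly distinguishable.** The protocol says only that they may be.
- **That predictable last picks show steering.** With one type left there is nothing to choose.
- **That allocation cannot be traced.** Serial numbers are recorded at distribution and matched to households on a net master list. What is not described is a pre-specified assignment to compare it with.
- **That no adjusted analysis is planned.** Multivariable models are planned, with location and socioeconomic status among the explanatory variables. But that variable list also includes net use and washing, which arise after allocation, and the between-brand test itself names only brand.

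**Conclusion.** The point holds as a vulnerability in a stated procedure. The interviewer picks a coded, possibly recognisable set by hand on arrival, with no concealment or pre-assigned list described, so allocation can be steered by what is visible of the household. The documents give no evidence that it was.

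The effect on the brand contrast is unknown. Under the assumed ranges it is 0.5 to 3 points of attrition, against a design difference of 5. The choice and predictability figures rest on reading the bundle as 5/5/5 and, for predictability, on one person knowing which types have been used. If several interviewers share a bundle, each may know less. The main point needs neither assumption.

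**What to change.** **In the design.** The type for each listed household should have been generated in R, which the study already uses to draw households. It should be blocked 15/15/15 by village, with sets pre-labelled for the household and a sequence for substitute households. This would leave 1,140 per product and 3,420 in total unchanged, at the cost of a list and labels. It can no longer be applied, because distribution is complete.

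**Now, in the analysis.**
- Make the primary brand comparison at each survey adjust for village and for fixed household covariates collected before handover: sleeping spaces, socioeconomic score and house type.
- Exclude variables that arise after allocation, such as net use and washing.
- Report baseline balance by product, and the product mix by interviewer and day as far as the questionnaire records allow. The article does not say whether interviewer and date are recorded.
- Keep the unadjusted comparison as a sensitivity analysis.

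The cost is a little more analysis work and some wording. The covariates are ones the study already plans to collect. Adjustment cannot remove steering on factors that were not measured, and the report should say so.
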